## **8 MEDICAL DEVICES**

### **8.1 FLOQSwab 552C.80**

**Description:** The FLOQSWAB 552C.80 is a self-vaginal swab with a marked breakpoint, manufactured by Copan Italia S.p.A.

**CE Marking and intended use:** The FLOQSwab 552C.80 is CE marked as a medical device Class IIa; licenced for use for self-collection of vaginal samples in home setting for HPV detection. As such the FLOQSwab will be used within its intended use in this trial.

**Storage and shelf life:** The FLOQSwab 552C.80 has a shelf life of 36 months and must be stored between 3-30 degrees Celsius.

**Supply:** Copan Italia will supply up to 45,000 swabs free of charge for the duration of the trial. As the self-sampling kits will be issued to women and GP practices from CFH Docmail, Copan will arrange supply to CFH Docmail at a frequency as agreed in the terms of the supply agreement. The number and frequency of shipments will depend on the availability of storage space at CFH Docmail.

**Recall:** In the event of a manufacturer recall; Copan Italia S.p.A will notify the King's CPTU trial team. The CPTU trial team will coordinate with CFH Docmail and all participating GP practices to organise recall of any unused swabs to the manufacturer.

## 8.2 Roche cobas 4800 System

**Description:** The cobas 4800 system is a complete end to end solution that integrates total nucleic acid isolation, automates PCR setup and performs real-time PCR. The cobas 4800 system consists of two linked instruments: the cobas x 480 for fully automated sample extraction and the cobas z 480 for fast and accurate real-time PCR.

**CE Marking and intended use:** The cobas 4800 System is CE marked as an in vitro diagnostic medical device. The system is intended to be used as a diagnostic or screening system providing sample preparation, amplification and detection of specific targets from human samples.

**Supply:** Health Services Laboratories will procure the cobas 4800 system from Roche. Roche will also supply at cost consumables for 10,000 (+/- 10%) samples.

### 8.2.1 Roche cobas 4800 HPV Test

**Description:** The cobas® 4800 Human Papillomavirus (HPV) Test is a qualitative in vitro test for the detection of Human Papillomavirus in patient specimens. The test utilizes amplification of target DNA by the Polymerase Chain Reaction (PCR) and nucleic acid hybridization for the detection of 14 high-risk (HR) HPV types in a single analysis.

The test specifically identifies HPV16 and HPV18 while concurrently detecting the other high-risk types (31, 33, 35, 39, 45, 51, 52, 56, 58, 59, 66 and 68) at clinically relevant infection levels. Specimens are limited to cervical cells collected in Roche Cell Collection Medium (Roche Molecular Systems, Inc.), cobas® PCR Cell Collection Media (Roche Molecular Systems, Inc.), PreservCyt® Solution (Hologic Corp.) and SurePath™ Preservative Fluid (BD Diagnostics-TriPath). Manufactured by Roche Molecular Systems, Inc.

#### CE Marking and intended use:

The cobas 4800 HPV Test is CE marked as an in vitro diagnostic medical device (according to the In-Vitro Diagnostic Medical Devices Directive 98/79/EC).

Indications for use of the cobas® 4800 HPV Test are:

- (a) *The cobas® 4800 HPV Test is indicated for use in screening patients with ASC-US (atypical squamous cells of undetermined significance) cervical cytology results to determine the need for referral to colposcopy.*
- (b) *The cobas® 4800 HPV Test is indicated for use in screening patients with ASC-US cervical cytology results to assess the presence or absence of high-risk HPV genotypes 16 and 18.*
- (c) *The cobas® 4800 HPV Test is indicated for use adjunctively with cervical cytology to assess the presence or absence of high-risk HPV types.*
- (d) *The cobas® 4800 HPV Test is indicated for use adjunctively with cervical cytology to assess the presence or absence of HPV genotypes 16 and 18.*
- (e) *The cobas® 4800 HPV Test is indicated for use as a first-line primary screening test to identify women at increased risk for the development of cervical cancer or presence of high-grade disease.*
- (f) *The cobas® 4800 HPV Test is indicated for use as a first-line primary screening test to assess the presence or absence of HPV genotypes 16 and 18.*

As such the cobas 4800 HPV test will be used **outside** of its licenced indication for the trial and will be considered to be exempt from the directive under the 'in-house exemption' to the Medical Devices Regulations 2002. Full details can be found in section

**Supply:** Health Service Laboratory will procure the cobas 4800 HPV test and associated reagents from Roche for analysis of 10,000 (+/- 10%) samples.

## 9 STATISTICAL CONSIDERATIONS

### 9.1 Sample size considerations

This is a feasibility trial of the implementation of a new self-sampling pathway that is not designed to detect a difference between two arms. Rather, to estimate the increase in coverage associated with offering self-sampling to nonattenders, therefore, formal power calculations are not appropriate. In

addition, the trial aims to recruit as many women as possible that the budget will allow. Our budget allows for a return of approximately 10,000 samples and issuing of circa 31,000 kits.

According to the NHAIS 2017/18 data available online from the National General Practice Profiles (<https://fingertips.phe.org.uk/profile/general-practice>), across the five CCGs included in our trial there are 212 GP practices and 190,579 women who are  $\geq 6$  months overdue for cervical screening. Assuming 50% (106/212) of GP practices agree to take part, there would be approximately 95,000 ( $0.50 \times 190,579$ ) eligible women (i.e. women aged 25-64 eligible for cervical screening who are overdue by at least 6 months).

### 9.1.1 Direct Mail-out

Assuming 106 GP practices recruit women for an average of 9 months (GP practices will recruit for a minimum of 6 months and a maximum of 12 months given that study set-up at each practice will be staggered over a 6 month period) and 20 women reach the 15 month anniversary at each practice each month, approximately 19,000 women will be sent kits during the trial. Table 2 below provides the expected 95% confidence intervals for various uptake levels over an average of 9 months recruitment period. We have estimated that 15% of women who receive a kit via direct mail-out will return a self-sample (i.e. ~2,800 women will return a self-sample over an average of 9m).

**Table 2 Expected 95% confidence intervals for different proportions of women who return a self-sample based on 106 GP practices over a 9-month average recruitment period**

| Uptake among those offered kits | 95%CI     |
|---------------------------------|-----------|
| 10%                             | 9.6-10.4  |
| 15%                             | 14.5-15.5 |
| 20%                             | 19.4-20.6 |
| 30%                             | 29.3-30.7 |

### 9.1.2 Opportunistic offering of self-sampling

With an estimated 106 GP practices participating, there would be some 95,000 ( $190,579 \times (106/212)$ ) women eligible for opportunistic offering of kits. Based on our previous studies(16, 37)) we estimate that ~60% (57,000) will consult their GP practice over 9-12 months, some 17,100 (30%) will be offered a self-sampling kit and of those offered, ~12,000 (70%) will accept. We estimate that a total of ~8,500 would return a self-sample for HPV testing (50% of those offered i.e.  $17,000 \times 0.5$ ). Therefore, the proportion of women  $\geq 6m$  overdue cervical screening who will return a sample when opportunistically offered a kit (i.e.  $\approx 8,500/17,000$ ) could be estimated with a 95% confidence interval of width  $\pm 1.0\%$ .

### 9.1.3 Questionnaire-based sub-study

As the trial is designed to be descriptive, a formal power calculation is not possible. A previous study in Westminster, London(18) had a survey response rate of 97% among the 6% of women who completed a self-sample kit, and just under 1% for those who did not send back a kit. We therefore expect a very low response rate in women who do not return the kit, making statistical comparisons between completers and non-completers inappropriate. However, we plan to explore demographic patterns of PAPM stage, previous barriers and confidence in completing the kit (e.g. by ethnicity and level of deprivation) within the completer and (to a lesser extent) the non-completer groups, and to do this, we anticipate needing a relatively large sample.

We have allowed for a high response rate (90% for kit completers; 10% for non-completers) to avoid under-funding. This would yield a sample of ~5,500 kit completers and ~2,500 non-completers but we anticipate the actual sample size is likely to be somewhat lower.

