| Inclusion Criteria  | 
 
• Women <math>\geq 25</math> and <math>\leq 64^*</math> years old, and
 
• Eligible for cervical screening under the NHS CSP in England, and
 
• At least 6 months overdue cervical screening; and
 
• Registered at a participating GP practice
 
                                                                                                                                                                                                                                                                                                                                                                                                                                                                                         |                 |
| Exclusion Criteria  | 
 
• Women unable or unwilling to provide informed consent
 
• Women under the care of colposcopy within the last 36 months and/or due for a test of cure (HPV test to confirm if a woman has been successfully treated after treatment for cervical abnormalities)
 
                                                                                                                                                                                                                                                                                                                                                                                                                                                                                       |                 |
| Planned sample size | 
We expect up to ~10,000 women will return a self-sample
 
Assumptions:
 
 
• ~50% (106/212) of eligible GP practices recruited
 
• 9 months average recruitment period at GP practices
 
• An estimated 31,000 participants will receive self-sampling kits: 
 
○ 19,000 via direct mail out
 
○ 12,000 kits accepted opportunistically in GP primary care
 
 
 
• Estimated uptake: 15% for direct mail-out and 50% of those offered opportunistically
 
                                                                                                                                                                                                                       |                 |

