**Table 3 Summary of anticipated sub-study sample**

|                                           |        |
|-------------------------------------------|--------|
| Total questionnaires sent:                | 31,000 |
| Total returned from kit completers (90%): | 5,580  |

|                                               |       |
|-----------------------------------------------|-------|
| Total returned from kit non-completers (10%): | 2,480 |
| Total questionnaires returned                 | 8,060 |

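### Table 3 of the questionnaire sub-study silently assumes that 20% of kits are returned, while the rest of section 9.1 plans 32% to 36%, so completers and total volume are understated

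*Protocol*

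**What the plan says.** Section 9.1 sets the scale of the trial: "Our budget allows for a return of approximately 10,000 samples and issuing of circa 31,000 kits". The trial summary agrees: "We expect up to ~10,000 women will return a self-sample". Section 7.10 closes active recruitment at a minimum of 10,000 returned kits or at 12 months, whichever comes first.

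The pathway estimates follow. For mail-out, section 9.1.1 expects that about "2,800 women will return a self-sample over an average of 9m", from about 19,000 kits. For the opportunistic offer, section 9.1.2 expects about 12,000 kits to be accepted and says: "We estimate that a total of ~8,500 would return a self-sample for HPV testing".

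Section 9.1.3 then plans the questionnaire sub-study. It cites an earlier London study with a 97% response among kit completers and "just under 1% for those who did not send back a kit". It adopts 90% and 10% as deliberately high rates so that the sub-study is not under-funded, and states: "This would yield a sample of ~5,500 kit completers and ~2,500 non-completers". It adds that the achieved sample will probably be a little smaller. Table 3 gives the exact figures: 31,000 questionnaires sent, 5,580 returned by completers, 2,480 by non-completers, 8,060 in all.

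**The concern.** Every kit carries one questionnaire, so the split of the 31,000 questionnaires between completers and non-completers is fixed by the kit return rate. Section 9.1.3 gives the two response rates but not the return rate. If the return rate behind Table 3 differs from the one used in the rest of section 9.1, both groups and the total are wrong even when the response rates are accepted as they stand.

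What is at stake is the planning of the sub-study: how many returned questionnaires must be paid for, entered and linked, and what sample a reader expects. The table is meant as a generous allowance, so an error that makes it too small defeats its purpose. No primary endpoint depends on it.

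**Working it through.** **Inputs (all Protocol)**
- Kits issued, and so questionnaires sent: 31,000 (section 9.1, Table 3)
- Questionnaire response: 90% of completers, 10% of non-completers (section 9.1.3)
- Planned returns: about 10,000 (trial summary, section 9.1); by pathway 2,800 + 8,500 = 11,300 (sections 9.1.1 and 9.1.2)

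**Step 1: reproduce Table 3.**
- Completers: 5,580 / 0.90 = 6,200
- Non-completers: 2,480 / 0.10 = 24,800
- 6,200 + 24,800 = 31,000, and 6,200 / 31,000 = 20.0%

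The table is reproduced exactly, but only with a 20% return rate. In section 9.1 that figure appears only as one illustrative row of Table 2, for mail-out uptake.

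**Step 2: compare with planned returns.**
- 10,000 / 31,000 = 32.3%
- 11,300 / 31,000 = 36.5%
- With 2,800 mail-out returns, 6,200 leaves 6,200 − 2,800 = 3,400 opportunistic returns, against about 8,500 in section 9.1.2. Rounding cannot explain the gap.

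**Step 3: recompute.** With R returns, completers = 0.90 × R and non-completers = 0.10 × (31,000 − R).

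| Returns R | Completers | Non-completers | Total | Total against 8,060 |
|---|---|---|---|---|
| 6,200 (implied by Table 3) | 5,580 | 2,480 | 8,060 | as stated |
| 10,000 | 9,000 | 2,100 | 11,100 | +3,040 (38% more) |
| 11,300 | 10,170 | 1,970 | 12,140 | +4,080 (51% more) |

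At 10,000 returns, completers are 9,000 / 5,580 = 1.61 times the stated number, and non-completers are 2,100 / 2,480 = 0.85 of it (15% fewer). At 11,300 returns, non-completers are 1,970 / 2,480 = 0.79 of it (21% fewer).

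**Step 4: try other readings.**
- The 50% opportunistic return applied to the 12,000 accepted kits instead of the 17,000 offers: 0.15 × 19,000 + 0.50 × 12,000 = 8,850 returns (28.5%), giving 7,965 + 2,215 = 10,180.
- 15% applied to all kits: 4,650 returns, giving 4,185 + 2,635 = 6,820.

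Neither reproduces Table 3.

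**Step 5: test the caveat that the sample will be smaller.** For completers to number 5,580 at the planned returns, their response would have to fall to 5,580 / 10,000 = 56% or 5,580 / 11,300 = 49%. The protocol assumes 90% and cites 97%. For completers the caveat points the wrong way.

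**Step 6: non-completers at the cited rate.** Taking just under 1% as 1%, 0.01 × 21,000 = 210 at 10,000 returns, and 0.01 × 19,700 = 197 at 11,300 returns. At 97% and 1% with 10,000 returns the total is 9,700 + 210 = 9,910, still 23% above 8,060, so the finding on total volume does not depend on the 10%.

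**The case against.** The best defence is that Table 3 is a disclosed budgeting device in a descriptive sub-study with no power calculation. Much of that stands, and it rules out several stronger readings.

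- A reader might infer that the 10% non-completer rate is a mistake and the non-completer sample fictitious. The documents do not support this. Section 9.1.3 prints the under-1% figure, expects a very low response and presents 10% as a deliberately high allowance. Section 4.5 also anticipates a low response in this group. The count of about 200 is a scenario carried over from one earlier study with 6% kit completion; here about 12,000 kits are accepted in person. What remains is that the table's title does not mark the figure as a ceiling, and that the caveat is mild for a possible tenfold gap.
- A reader might infer that non-completer analyses must be restricted. Section 9.1.3 already gives that group less weight, and section 9.2.4 makes demographic comparisons conditional on sample size. Section 3.2 does list a completer versus non-completer comparison that section 9.1.3 calls inappropriate, but that is a separate matter of wording which Table 3 does not settle.
- A reader might infer that the sub-study budget is short. The protocol gives no questionnaire budget or unit cost, and the 31,000 sent out do not change. Only the planning volume for returns is shown to be too low.
- The 51% excess, or about 12,000 questionnaires, should not be the headline. It needs 11,300 returns, above the 10,000 at which section 7.10 can close recruitment and slightly above the 11,000 upper limit of the test supplies in section 8.2 (10,000 plus 10%).

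It can also be said that 15% fewer non-completers falls within the stated caveat. That is fair for that group alone. None of this explains the 20% return rate or repairs the completer count.

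**Conclusion.** The planned sub-study sample is wrong as written. Table 3 and section 9.1.3 rest on 6,200 returned kits (20%), while the protocol elsewhere plans about 10,000 (32%), or 11,300 (36%) when the pathway estimates are added. At the protocol's own 90% and 10% response rates and 10,000 returns, completers are understated by 3,420 and the total by 3,040 (38% more than stated), while non-completers are overstated by 380. At 11,300 returns the corresponding differences are 4,590, 4,080 and 510.

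This assumes one questionnaire per kit and 31,000 kits, as Table 3 does. The trial summary treats 10,000 returns as an upper figure, but an allowance meant to prevent under-funding should cover it. The consequence is limited to sub-study planning and presentation. The completer error is on the safe side for precision: for a 50% item, 1.96 × √(0.25 / n) is about 1.3 points at n = 5,580 and 1.0 at n = 9,000.

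**What to change.** In section 9.1.3 and Table 3:

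- State the kit return rate used and tie it to section 9.1.
- Recompute from about 10,000 returns: 9,000 completers, 2,100 non-completers, 11,100 in total. Show 11,300 returns as the upper scenario: 10,170, 1,970 and 12,140.
- Label the 10% non-completer response as a funding ceiling, and show beside it about 200 non-completers if the cited rate of just under 1% applies.
- Reword the caveat so that it applies to non-completers and no longer suggests that completers will fall below 5,580.

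If 20% was in fact the intended return rate, the other parts of section 9.1 would need to be reconciled with it instead. The cost is a corrected table and a few sentences, plus a check that the handling of returned questionnaires is planned for about 11,100. No change to the analysis is needed.

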**Table 3 Summary of anticipated sub-study sample**

|                                           |        |
|-------------------------------------------|--------|
| Total questionnaires sent:                | 31,000 |
| Total returned from kit completers (90%): | 5,580  |

|                                               |       |
|-----------------------------------------------|-------|
| Total returned from kit non-completers (10%): | 2,480 |
| Total questionnaires returned                 | 8,060 |

## 9.2 Planned analysis

Overall baseline characteristics of individuals and GP practices will be presented overall and by pathway. We will identify the total number of women identified for the mail out cohort and the GP opportunistic pathway. We will also report on the cervical screening status at the end of the passive follow up period (aggregate data by GP practice).

We will compare individual characteristics for women who consent to take part in the trial vs. those who do not. We will also tabulate primary and secondary outcomes overall and by pathway.

A detailed description of analysis will be provided in the statistical analysis plan to be finalised prior to completion of data collection.

### 9.2.1 Primary endpoint

The primary outcome is uptake which is defined as the proportion of women who return a self-sample at 30 days, 90 days and at the end of the trial amongst those who have been given one direct mail out and opportunistic offer at GP practice with adjustment for multiple testing. We are interested in estimating variability across GP practice by using funnel plots(38) and estimating the intra cluster correlation (ICC).

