| To estimate the uptake and increase in coverage associated with offering self-sampling              | 
1. Uptake of kits at 30 days, 90 days and at the end of the trial*
 
2. Change in coverage at participating GP practices (when additionally counting a negative HPV test on a self-sample as having been screened) from the start vs the end of the trial.
 
3. Change in the proportion eligible appropriately screened.
 | 
1. Uptake: number of women screened by self-sample (at 30 days and 90 days from date kit mailed out (from print company) or given out in GP practice (GP records), and total) (from NHAIS and central laboratory) as a % of all women sent kit or opportunistically offered kit (from NHAIS for 15m and from GP record data for opportunistic)
 
2. Coverage: Age-appropriate coverage (as determined by the number of women who have either been screened by cytology or HPV negative on a primary HPV test or self-sample in the past 3.5y if aged 25-49 or 5.5y if aged 50-64y as a % of all those eligible for cervical screening) at participating GP practices. The endpoint is the change in coverage from the (practice-specific) beginning to the (practice-specific) end of the trial (all NHAIS data).
 
3. Eligible women (on the first of each month): women not ceased from screening aged 25-49 who have not been screened within the last 2.9 years or aged 50-64 and not screened within the last 4.9 years.
Appropriately screened: number of eligible women screened within the month. Data will be collected separately for "conventional screen", "return of mailout kit" and "return of opportunistic kit". The proportion eligible screened (by any approach) will be recorded each month during the trial and for the four months before the trial start. The average for the before and after period will be compared.
 |

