| To estimate the CIN2+ detection rate of self-sampling                     | Detection rates of disease (CIN2+) amongst women who return a self-sample                                                                    | Number of women with histologically confirmed CIN2+ (i.e. CIN2, CIN3 or invasive cervical cancer) in women who return a self-sample as a % of all women who return a self-sample (central laboratory data from the Cyres database)                                                                                                                                                                                                                                                                                                                                                                                                |
| To estimate the impact of self-sampling on colposcopy referral            | Rates of referral to colposcopy associated with self-sampling                                                                                | Number of colposcopy referrals as a % of all women who return a self-sample (from central laboratory Cyres)                                                                                                                                                                                                                                                                                                                                                                                                                                                                                                                       |
| To examine the uptake of self-sampling according to the mode of kit offer | Uptake of self-sampling kit within 6m after invitation when:
Sent kit directly (mail-out)

Vs

Offered kits opportunistically | Direct mail out: number of women returned self-sample as a % of total eligible sent kit directly (using data provided by NHAIS and mailing company)

Vs

Opportunistic: number of eligible women who returned a self-sample using opportunistic kit (data provided by NHAIS (sample "Source" field) as a % of total eligible women with Read codes for kits offered in GP records (GP record download)                                                                                                                                                                                                                |

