### 7.2.2 Opportunistic offering

Women targeted for opportunistic offering will be identified using the GP patient record software system (date of last recorded cervical screening test). Although cervical screening records in GP records are sometimes not up to date, this method of identifying the relevant cohort for opportunistic offering is currently the only viable option (GP patient records are not linked to the national screening database (NHAIS)).

An alert will be set up on the electronic patient record (EPR) software to automatically flag potentially eligible women when their record is opened. Specifically, EPR systems will be programmed to flag women aged 25.5-64 years who are at least 6 months overdue cervical screening (i.e. no cervical screening test (cytology, HPV primary or self-sample) recorded in the past 3.5 years (if aged 25-49) or 5.5 years (if aged 50-64) and no codes for hysterectomy or amputation of cervix). The alert will be switched on at the practice start date.

Doctors, nurses and healthcare assistants (HCA)/assistant practitioners (AP) will be asked to offer self-sampling kits to women who have been flagged when they consult for any reason. In practice, this will be on a case-by-case basis at the discretion of the healthcare professional consulted. The trial invitation (kit offer) will comprise a brief conversation (~2 minutes) at the end of the consultation. Healthcare professionals will be asked to confirm the women's eligibility before handing them a self-sampling kit, which includes the patient information booklet.

A study template will be set up in the GP electronic patient record system. When women are offered kits, the consulting health professional will use the template to record:

- 1) Whether or not the trial kit was accepted.

- 2) If accepted: trial kit ID number
- 3) If declined:
  - a) Reason for declining (if logistics allow)
  - b) Consent or dissent to share anonymous data from their GP records and the national cervical screening database

If the woman accepts a kit, the consulting health professional will:

- Print out a lab request/consent form with the woman's details mail-merged using the EPR system to be returned with the sample
- Write the kit ID number on the lab request/consent form
- Write three of the NHS CSP acceptable identifiers on the tube label. Preferably these will comprise the woman's name, date of birth and postcode.

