The coding of the dissent into the electronic patient record will allow YouScreen study EMIS searches to be programmed to exclude data with this code in trial reporting datasets (apart from aggregate reports which do not require permission).

The exclusion list managed by NHS Digital will be applied to all NHAIS machines to ensure that the NHS number of any woman on this list is removed from the YouScreen NHAIS searches to identify women at the 15m anniversary for mailout and from the trial reporting datasets (apart from aggregate reports).

GP Practices will be provided with instructions for managing the opt-out process for the study at the Site Initiation Visit.

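### Section 9.2.1 leaves open whether primary opportunistic uptake is per woman offered a kit (about 50%) or per woman given one (about 71%), and line-level GP extracts would probably bias it upward

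*Protocol*

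**What the plan says.** **Definition.** For primary endpoint 1, Protocol section 3.2 counts women screened by self-sample and expresses them "as a % of all women sent kit or opportunistically offered kit". The 30- and 90-day clocks start when the kit is mailed "or given out in GP practice (GP records"). For the secondary comparison by mode of offer, the opportunistic result is "as a % of total eligible women with Read codes for kits offered in GP records (GP record download"). Section 9.2.1 restates the primary outcome as the proportion of women who return a self-sample "at the end of the trial amongst those who have been given one direct mail out and opportunistic offer at GP practice", and adds an adjustment for multiple testing.

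**Data.** Under section 7.2.2 the practice template records, for a woman who declines, "Consent or dissent to share anonymous data from their GP records and the national cervical screening database". Under section 7.3.5 a dissent code lets the study's EMIS searches be programmed "to exclude data with this code in trial reporting datasets (apart from aggregate reports which do not require permission"). Section 10.4.4 repeats that the GP searches leave out women coded as opted out. Section 7.3.5 also offers the opt-out to any woman who does not return a sample, in either pathway. Section 7.9 keeps participants who withdraw in the uptake data. Section 7.3.1 has practices supply aggregate EMIS data for monthly reporting.

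**The concern.** The trial's headline number is defined in two places, and the wordings are not equivalent. If 9.2.1 means a kit handed over, women who decline leave the denominator. If it means an offer made, they stay.

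The numerators differ too. Under section 7.5.4 an invalid sample is neither analysed nor reported to NHAIS, so it has been returned although the woman has not been screened. The glossary entry for coverage explains screened as tested with a documented result.

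The clock in 3.2 adds to the uncertainty. A decliner has no date on which a kit was given out, so the text does not say how she enters the 30- and 90-day figures.

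The data rule raises a second problem. Whether a woman can leave the denominator depends on what she did. A decliner, or another non-returner, can be removed through a dissent code, whereas a woman who returned a sample and later withdraws stays in. Uptake computed from what remains would tend to be too high. Section 17 intends the findings as evidence for a new screening policy, so the basis of the uptake figure matters to its users.

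**Working it through.** **Inputs (Protocol 9.1.1 and 9.1.2).** 19,000 women mailed a kit with 15% uptake; 95,000 eligible for the opportunistic offer; 60% consult; 30% of those are offered a kit; 70% of those offered accept; returns are 50% of those offered.

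**Reproducing the plan's figures**
- Consulting: 95,000 × 0.60 = 57,000.
- Offered: 57,000 × 0.30 = 17,100.
- Accepting: 17,100 × 0.70 = 11,970, stated as about 12,000.
- Returning: 17,000 × 0.50 = 8,500, as stated.
- Plan's uptake: 8,500/17,000 = 50%, as stated.

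**Effect of the denominator**
- Per woman offered: 8,500/17,100 = 49.7%, about 50%.
- Per woman given a kit: 8,500/12,000 = 70.8%, about 71%.
- Mail-out returns: 19,000 × 0.15 = 2,850. Both pathways: 2,850 + 8,500 = 11,350.
- Pooled, sent or offered: 11,350/(19,000 + 17,100) = 11,350/36,100 = 31.4%.
- Pooled, sent or given: 11,350/(19,000 + 12,000) = 11,350/31,000 = 36.6%.

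The pooled figures treat the two pathways as separate women, although section 7.2.2 allows one woman to receive more than one offer.

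The gap for the opportunistic pathway is about 21 points. Section 9.1.2 states a 95% interval of ±1.0 point. The simple binomial half-width is 1.96 × √(0.25/17,000) = 0.75 points. Sampling error is small beside the choice of denominator on either figure.

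**Effect of removing dissenting decliners.** There are 17,000 − 12,000 = 5,000 decliners. Let *d* be the share who dissent. The protocol gives no value, so every *d* below is an assumption, and dissenters are assumed never to return a sample.

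Uptake = 8,500/(17,000 − *d* × 5,000)

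| *d* (assumed) | Denominator | Uptake |
|---|---|---|
| 0% | 17,000 | 50.0% |
| 10% | 16,500 | 51.5% |
| 25% | 15,750 | 54.0% |
| 50% | 14,500 | 58.6% |
| 75% | 13,250 | 64.2% |
| 100% | 12,000 | 70.8% |

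Opt-outs by women who took or were mailed a kit and did not return it would act in the same direction and are not in the table.

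**Multiple testing.** Section 9.2.1 names no method. As an illustration, Bonferroni over three time points multiplies the half-width by 1.22, from 0.75 to about 0.9 points.

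**The case against.** The best defence is that 9.2.1 is clumsy but not in conflict with 3.2. What was given can be read as the mail-out or the offer, and the sentence does not name a kit as its object. The Trial Summary, both uptake measures in 3.2, Table 2 in 9.1.1 and the text of 9.1.2 all count women sent or offered a kit. This stands as far as it goes: a reader might infer that 9.2.1 fixes a second denominator, and the text does not support that. It is ambiguous. But an ambiguity in the primary definition that is worth about 21 points still needs removing.

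On the data, section 7.3.5 exempts aggregate reports and section 7.3.1 already provides for them monthly. Section 3.2 says only that the opportunistic denominator comes from GP record data, without requiring line-level records. This also stands: the bias is avoidable. What is missing is a statement of which source is used.

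Two stronger readings go too far. One is that the exclusion can only raise uptake. Section 7.2.2 reports that women who declined in an earlier study accepted later offers, so a dissenting decliner who afterwards returns a sample could leave both numerator and denominator. The other is to quote a single biased value such as 59%. That needs about half of decliners to dissent, and no section gives a dissent rate.

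The numerator difference may be shorthand, since 3.2 itself speaks of returned samples when comparing modes of offer. Section 3.2 also plans, as exploratory and if data allow, the shares accepting and declining, which would help a reader convert between bases.

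**Conclusion.** The point holds as an ambiguity in the primary endpoint together with an unstated data source. On the protocol's planning figures, the reading of 9.2.1 moves opportunistic uptake from about 50% to about 71%, and pooled uptake from about 31% to about 37%. Whether the numerator is women screened or any sample returned is also unsettled; the documents give no figure from which to size that.

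Using line-level extracts for the denominator would probably bias uptake upward, by an amount that cannot be fixed from the protocol. If only decliners are removed, the result lies between 50% and 71%. This rests on two assumptions: that the dissent recorded on the decline template uses the same code as the opt-out in 7.3.5, which is an inference from the similar subject matter, and that few dissenting decliners later return a sample.

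The multiple-testing phrase is a minor matter. It is attached to estimated proportions without a stated hypothesis, and its likely effect on the intervals is small.

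**What to change.** 1. Make 9.2.1 repeat the section 3.2 definition. Denominator: distinct women sent a kit or recorded as offered one, each counted once because repeat offers are allowed. Numerator: women screened by self-sample, meaning those with a valid result.
2. Use the offer date as time zero for women who decline, and say which date applies when a woman has more than one offer.
3. State that the opportunistic denominator is taken from the aggregate EMIS reports, which keep dissenters, as a count of distinct women. Use line-level data for the models with covariates.
4. Report uptake per kit accepted, any sample returned, and the number of dissenters as supplementary figures.
5. Remove the adjustment for multiple testing from the uptake estimates, or say which tests it applies to.

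The cost is wording plus one aggregate count per practice per month from reports already planned. It is best settled before the EMIS searches are written.
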